| Healthcare Utilization Questionnaire |  |  |  |  |  |  | X | X | X |  |  |  | X |
| Rabies vaccine |  |  |  | (X) | (X) | (X) |  |  |  | (X) | (X) | (X) |  |
| Research blood collection^l^ | X |  | X |  |  |  | X |  |  |  |  |  | X |
| Vitamin A | X^m^ |  |  |  |  |  |  |  |  |  |  |  |  |

Abbreviations: AE, adverse event; HIV, human immunodeficiency virus; Ig, immunoglobulin; MUAC, mid-upper arm circumference; NP, nasopharyngeal; OP, oropharyngeal; PCR, polymerase chain reaction.

(X) = Each participant will receive only one 3-dose series of rabies vaccine according to randomization to early group (vaccination at Visits 2, 3, and 4) or late group (vaccination at Visits 8, 9, and 10).

^a^ EARLY rabies vaccination: Only participants randomized to EARLY rabies vaccine attend Visits 2, 3, 4. Visit 2 occurs 8 weeks after Day 0; Visit 3 occurs 7 days after Visit 2; Visit 4 occurs 21 to 28 days after Visit 2 AND at least 14 days after Visit 3.

^b^ LATE rabies vaccination: Only participants randomized to LATE rabies vaccine attend Visits 8, 9, 10. Visit 8 occurs 47 weeks after Day 0; Visit 9 occurs 7 days after Visit 8; Visit 10 occurs 21 to 28 days after Visit 8 AND at least 14 days after Visit 9.

^c^ Day 0 is defined as the day screening occurs and the first research blood sample is collected. Inclusion/exclusion criteria evaluation for enrollment will be completed when PCR and measles IgG/IgM and HIV results are available, generally by Day 14. In cases where the clinical presentation is consistent with measles but the Day 0 tests (measles PCR and measles IgM) are negative or equivocal, an optional retest of the measles IgM can be done between Days 7 and 10. The guardian/parent will be informed of the need for a retest and asked to bring the child back to the clinic. Blood will be collected via finger stick for the retest and results will be available by Day 14. All potential participants (or guardian/parent) will be informed of eligibility status by a designated study staff by phone, if possible, prior to the Day 14 scheduled study visit or at the Day 14 scheduled study visit. Ineligible participants may be invited to the site to discuss test results and referral for measles vaccination if serum IgG and IgM are both negative.

^d^ Vital signs include temperature, heart rate, and respiratory rate; may be obtained prior to rabies vaccine administration, if clinically indicated.

^e^ MUAC in children 12 to 59 months old.

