## Background

The continual measles outbreaks in West Africa underscore the importance of studies that will contribute to an understanding of the impact of MeV infection on the immune system and associated morbidity and mortality. Over the past decade, West Africa has experienced measles outbreaks each year. In Guinea, for example, the number of confirmed cases from January to June 2022 in 22 of 38 health districts was 2,299, 69% of which were in children aged 6-59 months.[[1](#_ENREF_1)] As another example, Mali recorded 218 cases in January 2022, and this is likely an underestimation.[[2](#_ENREF_2)] From January to October 2022, 7,927 suspected measles cases were reported from 9 of the 15 counties in Liberia; 93% (7,377) of these were confirmed through laboratory testing, clinically compatible with measles, and epidemiologically linked to other measles cases.[[3](#_ENREF_3)] These continued outbreaks have largely followed large-scale public health emergencies such as the Ebola epidemic and the current COVID-19 pandemic, which has disrupted global routine childhood vaccine coverage.[[4-6](#_ENREF_4)] Thus, measles outbreaks can be expected to continue in the coming years.

MeV can be serious and is one of the leading causes of death for children globally.[[7-9](#_ENREF_7)] MeV is highly contagious, and high vaccine coverage (above 90%) is essential to curb transmission.[[7](#_ENREF_7), [10](#_ENREF_10)] In addition to the seriousness of acute disease, there is a lasting impact of MeV infection. While MeV infection results in a strong immune response that confers life-long immunity, there is a prolonged increase in susceptibility to other infections, known as “immune amnesia,” following MeV infection.[[11](#_ENREF_11)] This immune amnesia has been associated with a loss of memory B cells and reduced antibody repertoires from previous infections and vaccinations.[[12](#_ENREF_12), [13](#_ENREF_13)] Measles immune amnesia has also been associated with clinical effects. A number of studies have shown that measles vaccination is associated with larger reductions in morbidity and mortality than would be expected from that caused by acute measles disease alone.[[14-19](#_ENREF_14)] Other studies have identified increased rates of infections and/or hospitalizations after measles virus infection.[[18](#_ENREF_18), [20-23](#_ENREF_20)]

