| To assess the appearance and continued production of B and T cells, especially ASCs from PBMCs in circulation following MeV infection in children 1-15 years old in a subset of participants, depending on availability of collected blood samples. | Mean change in cell number and functionality from baseline to 14 days. | Assessing the number and functionality of the B and T cells including ASCs will give insight into the impact of MeV on B cell development and humoral immunity. |
| To attempt to identify the etiology of illness in children who present with signs and symptoms consistent with measles and are screened but not enrolled due to negative measles PCR and IgM. | Unbiased next generation sequencing for pathogen discovery directly from the oropharyngeal (OP)/nasopharyngeal (NP) swab. | This may identify other pathogens that may mimic the clinical presentation of MeV in children who have symptoms but test negative. |
| To identify the genotypes of MeV collected in the study. | Next generation sequencing or targeted Sanger sequencing directly from the OP/NP. | This will allow identification of different genotypes of MeV in the countries enrolling participants. |
| To characterize the phenotype of the rash and/or Koplik spots in children who present with signs and symptoms consistent with measles who test positive for measles (PCR and/or IgM positive) and who test negative for measles (PCR and IgM negative). | Differences in rash patterns/presentation in children who test positive versus those who test negative for measles based on analysis of photographs. | This will allow for a comparison of rash and/or Koplik spot presentation in potential cases that end up testing positive or negative for measles in the laboratory. This will complement the exploratory objective of identifying the etiology via unbiased next general sequencing in the participants who test negative for measles. In addition, we can contribute images of measles rash on dark skinned children and Koplik spots to the medical literature. |

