Participants will undergo blood collection for screening and research testing at Day 0, between Days 7 and10 (optional, if Day 0 measles PCR and IgM are negative or equivocal in a child that presents with signs and symptoms consistent with measles), Day 14, Week 13, and Week 52. An upper respiratory specimen for MeV PCR will be collected at Day 0. Urine will be collected from females of reproductive potential to check for pregnancy at study visits with rabies vaccination or research blood collection. Hemoglobin levels will be checked at each study visit prior to research blood collection. Research samples will be tested for humoral and cellular immune responses to rabies vaccination (used as a controlled immune system stimulus, see section 8) and other research testing as described below (section 7.3). In addition, targeted sequencing will be performed on the measles virus to identify specific genotype. Unbiased sequencing will be used to try to identify the etiology in participants who have signs and symptoms consistent with measles but who test negative for measles by PCR and IgM. Optional photographs will be taken of the rash and/or Koplik spots at Day 0 to characterize the phenotype of the participants who test positive or negative for measles. We will also collect information on healthcare system encounters throughout the study period to help determine the clinical impact of immune amnesia after measles infection.

Participants with acute measles at screening/enrollment will be provided vitamin A treatment if they have not previously received it as part of their treatment. The treatment will follow WHO guidelines: 2 doses of 200,000 IU to be taken orally, 24 hours apart. The first dose will be given at the screening/enrollment visit, and the second dose will be given to the parent/guardian to be given the following day. A participant who has a rabies exposure during study participation will be provided rabies PEP with HRIG and rabies vaccine according to standard practice and the approved Verorab dosing schedule and depending on PrEP status. Any participant who receives rabies PEP prior to the timepoint that they were scheduled (randomized) to receive rabies PrEP under this study will continue in the study for follow-up visits but not receive PrEP according to their assigned randomization schedule. Data from these participants will be analyzed as described in Section [8.3](#_Population_for_Analysis).

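### Minor, exploratory objectives 2 and 4 only: the measles-negative group pools children never retested with those retested and negative, and un-retested equivocal children have no category

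*Protocol*

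**What the plan says.** Section 3 (Study Objectives) defines the objective 2 group as symptomatic children "screened but not enrolled due to negative measles PCR and IgM". The aim of sequencing them is stated as "This may identify other pathogens that may mimic the clinical presentation of MeV in children who have symptoms but test negative". The objective 4 endpoint is "Differences in rash patterns/presentation in children who test positive versus those who test negative for measles based on analysis of photographs". Positive there means PCR and/or IgM positive, and negative means both negative. Neither objective gives a time point, a retest condition or a rule for an equivocal result.

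Table 1 (Section 1.3) schedules the PCR swab once, at Day 0. IgM is taken at Day 0 and can be repeated at Visit 0.1. Footnote c gives the trigger as "In cases where the clinical presentation is consistent with measles but the Day 0 tests (measles PCR and measles IgM) are negative or equivocal" and then says that "an optional retest of the measles IgM can be done between Days 7 and 10". The next sentence of the footnote reads "The guardian/parent will be informed of the need for a retest and asked to bring the child back to the clinic". Section 4.1 (Overall Design) again describes the repeat as "optional, if Day 0 measles PCR and IgM are negative or equivocal in a child that presents with signs and symptoms consistent with measles", and the synopsis also calls it optional.

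Section 4.1 places the sites in areas with measles outbreaks. Section 2.2 (Background) reports 7,927 suspected cases in Liberia, of which "93% (7,377) of these were confirmed through laboratory testing, clinically compatible with measles, and epidemiologically linked to other measles cases".

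**The concern.** The retest is aimed at exactly the children who would form the negative group, so the protocol already accepts that Day 0 results may not settle their status. A child with measles who is missed at Day 0 and does not return is nevertheless labelled negative, on the same footing as a child with a second negative IgM. A child left equivocal and not retested is not placed at all under objective 4.

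Where most suspected cases are measles, few children are truly free of it, so even a low miss rate can supply a visible share of the negatives. In objective 4 this pulls the negative group's rash and Koplik appearance toward that of measles and shrinks any real difference. Objective 2 is descriptive, with no comparator. There the effect is that missed measles sits among the presumed mimics, which can raise the share with no cause found or lead to an incidental organism being credited. The protocol also intends to contribute images to the literature, so the labels matter beyond the trial.

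**Working it through.** **The protocol's figure.** 7,377 / 7,927 = 0.931, which reproduces the stated 93%.

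**Formula.** The share of the negative group that has measles is

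c = p(1 − s)(1 − u·r) / [p(1 − s)(1 − u·r) + (1 − p)]

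- p: share of screened suspects with measles. 0.931 is from Section 2.2; 0.70 and 0.50 are assumed.
- s: combined Day 0 sensitivity, meaning PCR or IgM positive. Assumed, 90% to 99%.
- u: share of Day 0 non-positive children who are retested. Assumed, 0 to 1.
- r: share of missed cases that the retest detects. Assumed, 0.8 or 0.9.
- Specificity is set to 1. The protocol gives none of s, u, r or specificity.

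**No retest (u = 0), s = 95%.**

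- p = 0.931: 0.0465 / (0.0465 + 0.0694) = 40%
- p = 0.70: 0.035 / (0.035 + 0.300) = 10%
- p = 0.50: 0.025 / (0.025 + 0.500) = 5%

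**No retest, range of sensitivities.**

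| s | p = 0.931 | p = 0.70 | p = 0.50 |
|---|---|---|---|
| 90% | 57.3% | 18.9% | 9.1% |
| 95% | 40.1% | 10.4% | 4.8% |
| 98% | 21.2% | 4.5% | 2.0% |
| 99% | 11.8% | 2.3% | 1.0% |

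To hold c at 10% without a retest, s must be at least 1 − (0.10/0.90)(1 − p)/p. That is 99.2% at p = 0.931, 95.2% at p = 0.70 and 88.9% at p = 0.50.

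**With retesting, s = 95%, p = 0.931.** Half retested with r = 0.9: 0.0465 × 0.55 = 0.0256, and 0.0256 / (0.0256 + 0.0694) = 27%. All retested: 6% with r = 0.9 and 12% with r = 0.8. The all-retested figures also describe a confirmed-negative stratum restricted to retested children, provided that returning is unrelated to true measles status.

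**Effect on objective 4.** If missed cases look like detected cases, the expected difference in a rash feature is (1 − c) times the true difference. At c = 40% it keeps 60% of its size; at c = 5% it keeps 95%.

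**The case against.** The best reply has four parts.

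- **Objective 4 compares test results, not true disease.** Group and endpoint match as worded. This stands as far as it goes, but the stated reason for the two objectives is to learn about illness that mimics measles, so the label still has to carry that meaning.
- **There is a safeguard.** Visit 0.1 exists, families are asked to return, and follow-up processes for suspected measles are left to the manual of procedures. Low uptake is therefore an assumption. This stands. A reader might infer that negative status rests on Day 0 alone, but the documents do not support that. Section 5.1 accepts a positive IgM without fixing a day, and retest results arrive by Day 14, so a positive retest reclassifies the child. The gap concerns only children not retested or still equivocal.
- **The split by retest status could be left to the analysis plan.** This is partly right. But the group is defined in the protocol's objectives, the two statements in footnote c need reconciling there, and no later plan can recover an IgM sample that was never drawn.
- **Sequencing may find the missed cases.** Section 7.3 allows unbiased sequencing of plasma as well as swabs, and a measles finding would also identify that child's photographs. This stands in part, since the swab is the same Day 0 specimen that was PCR negative. No rule says that such a finding changes the child's category.

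It is also tempting to quote a loss of power. The protocol plans no power for objective 4. At 93%, 128 confirmed cases would come with only about 10 non-measles children (128/0.931 − 128 ≈ 9.5, ignoring other exclusions), so a power claim would have no basis.

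**Conclusion.** The point holds as a minor one, confined to exploratory objectives 2 and 4. As written, never-retested children are pooled with retested negatives, and an un-retested equivocal child has no place in objective 4.

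The size is conditional. At an assumed 95% Day 0 sensitivity and no retest, missed measles would be about 40%, 10% or 5% of the negative group at a prevalence of 93%, 70% or 50%. The top figure uses one country's count, which mixes laboratory, clinical and epidemiological confirmation and need not match laboratory positivity among children screened for rash or Koplik spots. These shares show what is possible and are not estimates for this study.

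A reader might infer that the main comparisons are contaminated too. The documents do not support that: Section 5.1 requires controls to have no rash or Koplik spots, so symptomatic test-negative children do not enter the control group.

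**What to change.** In Section 3, for objectives 2 and 4:

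1. Define confirmed-negative as negative on Day 0 PCR, Day 0 IgM and Day 7-10 IgM.
2. Report children not retested, or still equivocal, as a separate unconfirmed stratum alongside the confirmed negatives and not pooled with them.
3. Count any measles virus found by sequencing as measles-positive for both objectives.
4. Reconcile the two descriptions of the retest in footnote c, optional in one sentence and needed in the next, and align the synopsis and Section 4.1.

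This uses a visit already in Table 1, adds no test and drops no child from reporting. It costs a wording change and one more column in the tables. The confirmed-negative group will be smaller, possibly very small, and may be selected by who returns. Showing the two strata side by side makes that visible.

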# INTRODUCTION

## Study Rationale

A phenomenon of depletion of pre-existing antibodies and increase in susceptibility to infections, known as “immune amnesia,” following MeV infection has been reported by several studies as described below (section 2.2). Ongoing recurrent outbreaks of measles in West Africa allow a more detailed evaluation of the pathophysiology of immune amnesia and how, it affects the incidence of subsequent infections.

In this study, we will assess whether MeV infection: 1) induces a loss of pre-existing immunity to pathogens prevalent in children in select African regions; 2) results in decreased immune responses to a controlled immune stimulus (rabies vaccination); and 3) is associated with an increase in healthcare system encounters in the year following MeV infection.

## Background

The continual measles outbreaks in West Africa underscore the importance of studies that will contribute to an understanding of the impact of MeV infection on the immune system and associated morbidity and mortality. Over the past decade, West Africa has experienced measles outbreaks each year. In Guinea, for example, the number of confirmed cases from January to June 2022 in 22 of 38 health districts was 2,299, 69% of which were in children aged 6-59 months.[[1](#_ENREF_1)] As another example, Mali recorded 218 cases in January 2022, and this is likely an underestimation.[[2](#_ENREF_2)] From January to October 2022, 7,927 suspected measles cases were reported from 9 of the 15 counties in Liberia; 93% (7,377) of these were confirmed through laboratory testing, clinically compatible with measles, and epidemiologically linked to other measles cases.[[3](#_ENREF_3)] These continued outbreaks have largely followed large-scale public health emergencies such as the Ebola epidemic and the current COVID-19 pandemic, which has disrupted global routine childhood vaccine coverage.[[4-6](#_ENREF_4)] Thus, measles outbreaks can be expected to continue in the coming years.

MeV can be serious and is one of the leading causes of death for children globally.[[7-9](#_ENREF_7)] MeV is highly contagious, and high vaccine coverage (above 90%) is essential to curb transmission.[[7](#_ENREF_7), [10](#_ENREF_10)] In addition to the seriousness of acute disease, there is a lasting impact of MeV infection. While MeV infection results in a strong immune response that confers life-long immunity, there is a prolonged increase in susceptibility to other infections, known as “immune amnesia,” following MeV infection.[[11](#_ENREF_11)] This immune amnesia has been associated with a loss of memory B cells and reduced antibody repertoires from previous infections and vaccinations.[[12](#_ENREF_12), [13](#_ENREF_13)] Measles immune amnesia has also been associated with clinical effects. A number of studies have shown that measles vaccination is associated with larger reductions in morbidity and mortality than would be expected from that caused by acute measles disease alone.[[14-19](#_ENREF_14)] Other studies have identified increased rates of infections and/or hospitalizations after measles virus infection.[[18](#_ENREF_18), [20-23](#_ENREF_20)]

Previous studies characterizing MeV immune amnesia have primarily been centered around a European population and rhesus macaques.[[24](#_ENREF_24)] Given the current outbreaks of measles in West Africa and recurrence of infectious diseases in pediatric populations, there is interest in determining whether measles-induced immune amnesia occurs in these African regions where tuberculosis, parasitic diseases (such as malaria), and arthropod-borne viruses (such as yellow fever and dengue) are endemic, and if so, what the mechanisms are that drive immune amnesia. The hypothesis of this study is that acute MeV infection induces a loss of pre-existing immunity to pathogens prevalent in select African regions. Compared to those who do not have acute MeV infection, acute MeV infection will result in:

1. A loss of total antibody diversity from previous infections and/or vaccinations compared to baseline.
2. Altered immune response to a controlled immune stimulus (rabies vaccination).
3. Increased incidence of illnesses or healthcare encounters in the year following acute MeV infection.

## Risk/Benefit Assessment

### Known Potential Risks

Blood draws: Drawing blood may cause pain, bruising, lightheadedness, possible fainting, local discomfort, uncontrolled bleeding, and, rarely, infection at the site where the needle is inserted. The study staff will evaluate injuries related to research blood draw and provide appropriate first aid and referral for care as needed.

Urine collection: There is no risk from urine collection.

Upper respiratory specimen: The risks of obtaining a respiratory swab through the oropharynx/ nasopharynx include ear, nose and throat discomfort and pain, headache, rhinorrhea, anxiety, and gagging. In rare cases a mild and self-limiting epistaxis may occur after nasopharyngeal swabbing.

Rabies vaccination: Soreness, redness, swelling, or itching at the site of the injection, and headache, nausea, abdominal pain, muscle aches, or dizziness can happen after rabies vaccine. Hives, pain in the joints, or fever sometimes happen after each vaccine dose. People sometimes faint after medical procedures, including vaccination. As with any medicine, there is a very remote chance of a vaccine causing a severe allergic reaction, other serious injury, or death.

Measles vaccination: The main risks associated with measles vaccination are pain, redness, swelling or itching at the injection site. The measles vaccine has been associated with a very low risk of febrile seizures that are not associated with any long-term effects. Some people may experience swelling in the cheeks or neck. A temporary low platelet count can rarely occur, which can cause a bleeding disorder that usually goes away without treatment and is not life-threatening. In very rare cases, a person may have a severe allergic reaction. People sometimes faint after medical procedures, including vaccination. As with any medicine, there is a very remote chance of a vaccine causing a severe allergic reaction, other serious injury, or death. Anyone who has ever had a life-threatening allergic reaction to the antibiotic neomycin, or any other component of the measles vaccine should not receive the vaccine.

Vitamin A: When administered orally per World Health Organization (WHO) guidelines, sides effects are rare; mild symptoms typically develop within 24 hours and can include loose stools, headache, irritability, fever, nausea, and vomiting; these are reversible within 24 to 48 hours upon discontinuation of vitamin A.[[25](#_ENREF_25)] An acute intoxication typically occurs if more than 100 times the recommended dietary allowance of 10,000 IU is ingested; signs and symptoms occur within days to weeks of ingestion and typically include severe headache, blurred vision, nausea, dizziness, aching muscles, and coordination problems.[[26](#_ENREF_26)] In severe cases, cerebral spinal fluid pressure can increase, leading to drowsiness and, eventually, coma and even death.[[26](#_ENREF_26), [27](#_ENREF_27)]

Human rabies immune globulin (HRIG): Very mild and transient local reactions at the injection site such as pain and inflammation and systemic reactions such as headache, low grade fever, gastrointestinal disturbances, joint pain, and very rarely anaphylactic reactions, have been reported after receiving HRIG.[[28](#_ENREF_28), [29](#_ENREF_29)]

Confidentiality: There is a slight risk of loss of confidentiality, but every effort will be made to keep research information confidential as described in section [9.4.](#_Confidentiality_and_Privacy)

Photographic images: Taking pictures of the face and body may be embarrassing to some people. These photographs may be used for teaching or education purposes, as well as for future research projects by the study team or other researchers. They may also be published in medical journals, without identifying the participant. We will attempt to preserve the anonymity of the participant as much as possible, while providing the information needed to support the research being published. Photographs will be stored securely, but there is a slight risk of loss of confidentiality.

